## Abstract

**Introduction:**

In Australia, only 22% of male and 8% of female adolescents meet the muscle-strengthening physical activity guidelines, and few school-based interventions support participation in resistance training (RT). After promising findings from our effectiveness trial, we conducted a state-wide dissemination of the ‘*Resistance Training for Teens*’ (RT4T) intervention from 2015 to 2020. Despite high estimated reach, we found considerable variability in programme delivery and teachers reported numerous barriers to implementation. Supporting schools when they first adopt evidence-based programmes may strengthen programme fidelity, sustainability, and by extension, programme impact. However, the most effective implementation support model for RT4T is unclear.

**Objective:**

To compare the effects of three implementation support models on the reach (primary outcome), dose delivered, fidelity, sustainability, impact and cost of RT4T.

**Methods and analysis:**

We will conduct a hybrid type III implementation–effectiveness trial involving grade 9 and 10 (aged 14–16 years) students from 90 secondary schools in New South Wales (NSW), Australia. Schools will be recruited across one cohort in 2023, stratified by school type, socioeconomic status and location, and randomised in a 1:1:1 ratio to receive one of the following levels of implementation support: (1) ‘low’ (training and resources), (2) ‘moderate’ (training and resources+external support) or ‘high’ (training and resources+external support+equipment). Training includes a teacher workshop related to RT4T programme content (theory and practical sessions) and the related resources. Additional support will be provided by trained project officers from five local health districts. Equipment will consist of a pack of semiportable RT equipment (ie, weighted bars, dumbbells, resistance bands and inverted pull up bar stands) valued at ~$A1000 per school. Study outcomes will be assessed at baseline (T0), 6 months (T1) and 18 months (T2). A range of quantitative (teacher logs, observations and teacher surveys) and qualitative (semistructured interviews with teachers) methods will be used to assess primary (reach) and secondary outcomes (dose delivered, fidelity, sustainability, impact and cost of RT4T). Quantitative analyses will use logistic mixed models for dichotomous outcomes, and ordinal or linear mixed effects regression models for continuous outcomes, with alpha levels set at p<0.025 for the outcomes and cost comparisons of the moderate and high support arms against the low support arm.

**Ethics and dissemination:**

Ethics approval has been obtained from the University of Newcastle (H-2021-0418), the NSW Department of Education (SERAP:2022215), Hunter New England Human Research Ethics Committee (2023/ETH00052) and the Catholic Schools Office. The design, conduct and reporting will adhere to the Consolidated Standards of Reporting Trials statement, the Standards for Reporting Implementation Studies statement and the Template for Intervention Description and Replication checklist. Findings will be published in open access peer-reviewed journals, key stakeholders will be provided with a detailed report. We will support ongoing dissemination of RT4T in Australian schools via professional learning for teachers.

**Trial registration number:**

ACTRN12622000861752.

STRENGTHS AND LIMITATIONS OF THIS STUDYOur study will test three implementation support models on a range of implementation outcomes and determinants using a hybrid type III implementation–effectiveness trial.Local health district staff (ie, project officers) are well placed to support the implementation of school-based interventions, but few studies have examined their capacity to support secondary schools.There is potential for secondary school teachers to deliver Resistance Training for Teens with poor fidelity.Our study does not include a control condition, but the low support group will serve as a ‘usual practice’ comparator.Student-level data will only be collected in a subset of schools by secondary teachers, which may compromise internal validity.

## Introduction

Physical inactivity has been described as a global health issue and is the fourth leading cause of premature death worldwide.^1^ The WHO recommends children and adolescents participate in 60 min of (predominantly aerobic) moderate-to-vigorous physical activity (MVPA) daily, as well as muscle strengthening activity at least 3 days per week.^2^ Despite these recommendations, physical activity declines substantially throughout adolescence, resulting in many adolescents failing to meet daily physical activity guidelines.^3^ Fewer than 1 in 50 Australian adolescents (15–17 years old) meet MVPA and muscle strengthening activity recommendations.^4^ Poor rates of muscle strengthening activity may explain the secular decline in muscular fitness (ie, strength, power and endurance) of Australian youth over the past 30 years,^5^ with a similar decline seen internationally.^6 7^ Muscular fitness is associated with various markers of health and well-being among children and adolescents in both cross-sectional^8^ and prospective^9^ studies. This prompted our team to investigate the key role of muscle strengthening activity during the school years.

Resistance training (RT) is a specialised form of muscle strengthening activity. It can be performed with or without equipment using a variety of resistive loads, and in a range of settings (eg, at home, school, local park or gym/fitness centre).^10^ When performed routinely, RT may lead to muscle hypertrophy (ie, increase in muscle size), improved muscular fitness (ie, muscle strength, power and/or endurance), body composition (ie, increases in fat-free mass and reductions in fat mass) and mental health (ie, self-esteem) in school-aged youth.^11^ RT is also recommended within global physical activity guidelines for adults,^1^ as it benefits a wide range of physical and mental health outcomes (including risk of chronic disease and depression/anxiety). However, the performance of RT is often perceived as more complex than aerobic activities (eg, walking and jogging). This may explain why participation in RT is much lower than for MVPA during adulthood.^2^ Gaining the knowledge, skills and confidence to participate in RT sets children and adolescents up for participation in RT across the lifespan.^12^ However, for decades, a number of myths and misconceptions about the safety and appropriateness of strength training have prevented it from being offered to most school-aged youth.^12^ Furthermore, among adults, there are a number of reported barriers to participation in RT, including lack of confidence,^13^ low self-efficacy,^13^ lack of time^14^ and perceived lack of access to necessary equipment.^14^ These barriers may also be present for adolescents, as they likely lack the knowledge, skills and/or confidence to engage in RT despite their desire to try a broader range of physical activities.^15^ It is therefore necessary that adolescents are provided with ample opportunities to develop the skills, knowledge and confidence to engage in RT.

Schools are effective settings for health promotion as they provide access to most children and adolescents, and have the facilities, equipment and qualified staff needed to deliver interventions.^16–18^ However, few school-based interventions provided adolescents with the confidence and competence to participate safely in RT^19^ and no prior studies have done so at scale.^19 20^ ‘Scale-up’ is defined as the ‘deliberate effort to increase the impact of successfully tested health interventions to benefit more people’.^21^ Few physical activity interventions have progressed beyond efficacy testing and no studies investigating scaled up RT interventions among secondary students appear within the extant literature.^22^ The WHO has advised policy-makers, funders and researchers to focus their efforts on scaling up evidence-based physical activity programmes while exploring various models of implementation.^23^ Prior to investing in scale-up, evaluating the effectiveness of models of implementation to inform future scale-up is necessary to guide the efficient use of resources. ‘Voltage drop’ refers to diminishing effectiveness when programmes are implemented at larger scale.^24 25^ Evaluating different models of implementation will help to minimise this phenomenon.

Resistance Training for Teens (RT4T) is an evidence-based programme designed to provide adolescents with foundational knowledge about RT and enhance competence, confidence and motivation to engage in RT across the lifespan. It was also designed to align with the Australian Curriculum for Health and Physical Education to develop the movement skills and concepts that will enable students to participate in physical activities that contribute to their health and well-being.^26^ We conducted a rigorous evaluation of the RT4T intervention using a cluster randomised controlled trial in 16 schools (n=607) between 2015 and 2016.^27^ The intervention resulted in immediate and sustained improvements in upper body muscular fitness and RT skill competency, demonstrating an effective and scalable approach to delivering RT within secondary schools. During this period, we established a partnership with the New South Wales (NSW) Department of Education to scale-up the programme. With support from the NSW Department of Education, 468 teachers from 249 NSW Government schools were trained to deliver the programme.^27^ We estimate that the programme reached ~10 000 students between August 2015 and October 2020. However, interviews conducted with a sample of teachers (n=19) who delivered RT4T, identified considerable variability in programme delivery. Also, several barriers to implementation emerged that included lack of support, motivation and time,^28^ impacting on programme fidelity and potential sustainability.

Implementation support, typically used for school physical activity programmes, is often criticised as being a ‘train and forget’ model. It comprises initial training workshops followed by limited ongoing support for schools. This approach is unlikely to address the primary impediments to programme implementation, but may explain some shortcomings in whether evidence-based health promotion programmes are adopted, implemented or maintained within schools. The most effective approach that optimises implementation fidelity and may sustain efficacious programmes over the longer term remains unclear.^29^ Therefore, the aim of the present trial is to evaluate the effects of three implementation support models on the reach, effectiveness, dose delivered, fidelity, adoption, sustainability, impact and cost of RT4T.

## Methods

### Experimental design

We will use a hybrid type III implementation–effectiveness trial design^30^ to evaluate the implementation and effectiveness of the RT4T intervention. We aim to recruit 90 secondary schools and randomise them to one of three groups: (1) low, (2) moderate or (3) high implementation support. The low support group will act as a control group (usual practice). This is the professional development model traditionally used by the NSW Department of Education and the delivery model used for RT4T from 2015 to 2020. In Australia, the academic year is separated into four ‘terms’ of 10 weeks duration. Following training, teachers enrolled in our study will deliver the 8-week RT4T intervention within one (or more) of two school terms (ie, within 6 months post-training). This provides teachers with some flexibility regarding the delivery period for RT4T within their academic year.

Regarding the timeline for the evaluation of the intervention, study assessments are undertaken at baseline, 6-month and 18-month follow-up. Teachers will be encouraged to continue delivering the programme after our research has concluded. Our implementation trial is guided by expert recommendations^31^ and is registered with the Australian New Zealand Clinical Trials Registry (ACTRN12622000861752). The design, conduct and reporting will adhere to the Consolidated Standards of Reporting Trials^32^ statement, the Standards for Reporting Implementation Studies^33^ statement and the Template for Intervention Description and Replication checklist.^34^

### School recruitment and selection

Secondary schools (government, Catholic and independent) in five local health districts in NSW (Illawarra Shoalhaven, Northern NSW, South Eastern Sydney, Sydney and Western NSW) will be eligible to participate in this study. Schools outside these districts will be able to attend the professional learning workshops and implement RT4T, but will not be included in the study to assess implementation outcomes. Eligible schools will be those that include students in grades 9 and 10 (aged 14–16 years). We will use a range of evidence-based recruitment and retention strategies to maximise participation and minimise dropout (at both school and teacher levels), including promotion within the NSW Department of Education School Sport Unit newsletter. This will include prenotification, the use of a dedicated recruitment coordinator, repeated reminders and deployment of staff from local health promotion teams to engage with schools.

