### Primary and secondary outcomes

A range of quantitative and qualitative methods will be used to assess primary and secondary outcomes at baseline (T0), 6-month (T1) and 18-month follow-up (T2). Our primary outcome is reach, operationalised as the proportion of grade 9 and 10 students from the study schools who participate in the RT4T programme. The proportion will be calculated as a percentage of students from grades 9 and 10 who participate in ≥50% of the RT4T practical sessions divided by the total number of students in grades 9 and 10 at the study schools. Secondary outcome measures include dose delivered, fidelity, sustainability, impact, cost-effectiveness and implementation determinants.

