#### Primary implementation outcome

##### Reach

Our primary outcome is reach, operationalised as the proportion of grade 9 and 10 students from the study schools who participate in the RT4T programme. The proportion will be calculated as a percentage of students from grades 9 and 10 who participate in ≥50% of the RT4T practical sessions divided by the total number of students in grades 9 and 10. We will assess reach by collecting teacher logbooks (ie, attendance lists) at T1 and T2. We have used logbooks previously in school-based health promotion trials^47 48^ and achieved high completion rates, high validity and reliability.^49^ A research team member will request that school champions provide a copy of teacher logbooks.

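### Schools trained in the 2015–2020 RT4T roll-out can enrol, but prior training and current delivery are not recorded or used in the reach comparison, and no T0 source for reach is described

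*Protocol article*

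**What the plan says.** **Eligibility.** Under School recruitment and selection, the pool is "Secondary schools (government, Catholic and independent) in five local health districts in NSW", and "Eligible schools will be those that include students in grades 9 and 10 (aged 14–16 years". No other condition on schools is stated, and earlier involvement with RT4T is not mentioned.

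**Earlier roll-out.** The Introduction reports that "468 teachers from 249 NSW Government schools were trained to deliver the programme" and adds: "We estimate that the programme reached ~10 000 students between August 2015 and October 2020". Experimental design says that the low support arm is the delivery model used in those years.

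**Strata and analysis.** Blinding and randomisation names three strata: school type, socioeconomic status and location. Statistical analysis compares reach between arms with school-level t-tests and names two moderators, school socioeconomic status and location. Prior RT4T training appears in neither section.

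**Timing of the primary outcome.** Primary and secondary outcomes says that the methods will "assess primary and secondary outcomes at baseline (T0), 6-month (T1) and 18-month follow-up (T2". The Reach section is narrower: "We will assess reach by collecting teacher logbooks (ie, attendance lists) at T1 and T2". Its definition counts every grade 9 or 10 student who attends at least half of the practical sessions, whatever led the school to deliver them.

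**Rationale and objective.** The abstract's background says: "Supporting schools when they first adopt evidence-based programmes may strengthen programme fidelity, sustainability, and by extension, programme impact". The objective is "To compare the effects of three implementation support models on the reach (primary outcome), dose delivered, fidelity, sustainability, impact and cost of RT4T", with no restriction to first adopters.

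**The concern.** A school trained between 2015 and 2020 may bring trained teachers, existing materials and possibly a programme still running. Any such delivery enters the numerator of reach in the same way as delivery prompted by the allocated support. With no T0 value for reach and no marker of prior training, the analysis cannot tell the two apart.

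Three consequences are possible:

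- **More variance.** If experienced schools have higher reach in every arm, schools differ more from one another and the t-test loses precision.
- **Chance imbalance.** Prior training is not a stratum, so arms of 30 schools can differ in their share of experienced schools.
- **Dilution.** If support adds less in experienced schools, the average difference shrinks, and a null result is hard to read.

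The low arm is also affected. A previously trained school in that arm receives the same delivery model a second time.

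**Working it through.** **Inputs (Sample size calculation).** 30 schools per arm, 20% without usable data, reach of 12.5% against 25%, SD 12 points, alpha 0.025, power 90%. Sidedness is not stated; two-sided is assumed.

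**Step 1: reproduce the plan.** By the normal approximation, n per arm = 2 × (2.241 + 1.282)² × (12 / 12.5)² = 22.9, so 23. Dividing by 0.8 gives 28.75, so 29, close to the stated 30. Usable schools: 30 × 0.8 = 24 per arm. The noncentrality is 12.5 / (12 × √(2/24)) = 3.61, and t-test power is 0.90. The sample size is not in error.

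**Step 2: assumptions.** Let f be the share of previously trained schools among those enrolled. The article gives neither f nor the size of any carry-over. I take f from 10% to 50% as an assumption. All power figures below are for the t-test with 24 schools per arm.

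**Step 3: equal carry-over, full support effect.** If earlier training adds c points to reach in every arm, the difference stays at 12.5. Only the SD changes: SD = √(144 + f(1 − f)c²).

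| f | SD, c = 4 | Power | SD, c = 12.5 | Power |
|---|---|---|---|---|
| 10% | 12.06 | 0.89 | 12.57 | 0.87 |
| 20% | 12.11 | 0.89 | 13.00 | 0.84 |
| 30% | 12.14 | 0.89 | 13.30 | 0.82 |
| 50% | 12.17 | 0.89 | 13.53 | 0.81 |

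**Step 4: support works less well in trained schools.** The SD is kept at 12. The difference is 12.5 × (1 − f/2) if the effect there is halved, and 12.5 × (1 − f) if it is absent.

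| f | Difference, half effect | Power | Difference, no effect | Power |
|---|---|---|---|---|
| 10% | 11.88 | 0.86 | 11.25 | 0.82 |
| 20% | 11.25 | 0.82 | 10.00 | 0.71 |
| 30% | 10.63 | 0.77 | 8.75 | 0.59 |
| 50% | 9.38 | 0.65 | 6.25 | 0.31 |

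In the no-effect case, letting the SD rise for the mixture of schools (12.3 to 12.8) lowers power a little further, to 0.80 at 10% and 0.28 at 50%.

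**Step 5: chance imbalance.** Under simple randomisation, the SD of the between-arm difference in f is √(2f(1 − f)/30): 0.077, 0.103, 0.118 and 0.129 at 10, 20, 30 and 50%. With c = 12.5 and f = 50%, one SD of imbalance moves the contrast by 12.5 × 0.129 = 1.6 points; with c = 4 and f = 20%, by 4 × 0.103 = 0.4 points. The inflated SDs in Step 3 already carry this uncertainty, so it is not an additional loss.

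**Step 6: how large could carry-over be?** The Introduction's own figures give 10 000 / 249 ≈ 40 students per trained school over about five years, or about 8 per school-year. That points to the small end of Step 3. Carry-over would run through teachers and schools: a grade 10 student in 2023 was in grade 7 in 2020.

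**The case against.** **Carry-over is not shown to occur.** The article does not say how many of the 249 schools lie in the five districts, how many might enrol, or whether any still deliver. About 8 students per school-year, reports of variable delivery and a gap of more than two years all suggest that little carries over. This stands, and it is why the likely loss of power is small.

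**Equal carry-over does not bias the comparison.** A reader might infer that existing delivery pulls both contrasts with the low arm towards zero. It does so only if support adds less in experienced schools. The article gives some reason to expect otherwise: teachers who had delivered RT4T named lack of support among the barriers, and the strategies were built on those findings. Planned reach of 12.5–25% is also far from a ceiling.

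**First adoption is not the estimand.** A reader might take the abstract's background sentence to mean that first adopters are the target population. The objective and the aim do not say so. Making first adopters the main analysis would also be costly: at a 30% share about 17 usable schools per arm remain (power 0.75), and at 50% there are 12 (power 0.57), for the full 12.5 points.

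**Stratification may help in part.** The roll-out was in government schools. If school type means sector, stratifying by it balances some of the prior training, and the figures in Step 5 are then upper values.

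**This is a condensed article.** Covariates and survey items may be set out in documents not shown. That limits the criticism of omitted detail. But the entry rule, the strata, the t-test and the timing of reach are all stated here, and the two statements on timing disagree.

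**Conclusion.** The point holds in a limited form. Previously trained schools can enrol, nothing stated in the article identifies or adjusts for them, and no T0 data source for reach is described although one section says primary outcomes are assessed then. It would go too far to say that reach has no baseline measurement: the article contradicts itself on this, and the sections need reconciling.

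Randomisation protects against systematic bias. What is at risk is precision, chance imbalance and the reading of a null result. If carry-over is equal across arms, power falls from 0.90 to about 0.89 (4 points) or to 0.87–0.81 (12.5 points) for a 10–50% share. The fall to 0.31 needs both a 50% share and no support effect in trained schools; the article supports neither assumption. All these figures rest on assumed shares and carry-over, two-sided alpha 0.025, and 24 usable schools per arm. This is a cheap improvement to the design, not a flaw that undermines the trial.

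**What to change.** 1. Check each enrolled school against the 2015–2020 training records and classify it as previously trained or not.
2. Add one item to the existing T0 teacher survey, answered before allocation is known: is RT4T currently being delivered, and to what share of grade 9–10 classes?
3. Reconcile Primary and secondary outcomes with Reach, so that the time points agree and T0 reach has a named source.
4. Replace the unadjusted t-test on reach with a school-level linear model that adjusts for prior training and T0 reach. Keep the alpha of 0.025 for each comparison with the low arm.
5. Prespecify the result in first adopters as a subgroup or sensitivity analysis, with all enrolled schools remaining the main estimate.

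**Cost.** A look-up in the roll-out records, one survey item, and one or two degrees of freedom. No additional schools are needed. The T0 item would be a teacher report by class, so it is a coarser measure than the logbook count at T1 and T2; it serves as a covariate, not as a like-for-like baseline.
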